### Data analysis

All data will be entered and analysed in Microsoft Excel. The cost per unit of each activity will be estimated by multiplying the incremental resource use with the corresponding unit prices. The proportional distribution of resources across activities will also be assessed. Total costs will be calculated by combining the frequency of each activity with its respective per-unit cost. In addition to total and activity-specific costs, cost-effectiveness will be assessed by calculating the incremental cost per unit reduction in Patient Health Questionnaire-9 (PHQ-9) and Perceived Stress Scale-10 (PSS-10) scores.

### Data governance (management, confidentiality, security, and quality control)

Personal data of research participants will be collected but subsequently anonymized. Every participant will be assigned a unique study ID, and only anonymized data will be input into the study’s primary database on the designated analysis computers. The original identifiable information, alongside a reference sheet linking study IDs to the initial data, will be separately saved in a password-secured folder on an encrypted hard drive, ensuring maximum safety. Access to this data will be exclusive to the site principal investigators (PI) and the data manager. Anonymized data will be retained in password-secured directories on analysis computers, with only the PI, Co-Investigators (Co-Is), and specific research personnel having access rights. Primary materials such as FGD transcripts, interview recordings, and collected surveys and questionnaires will be preserved for a span of 5 years post-study, adhering to standard guidelines. A comprehensive data management guide will be crafted detailing the procedures for data handling, storage, and accessibility. Study data will be collected and managed using REDCap electronic data capture tools hosted at Indian Council of Medical Research, headquarters (62, 64). Each site investigator will be tasked with ensuring the data is updated on a weekly basis.

### Monitoring and evaluation

The monitoring and evaluation (M&E) framework uses the logical framework approach, drawing the logical link between activities and inputs to the output and outcomes, to reflect the impact. The M&E indicators will be specifically defined. The indicators are numbered measurements that help track progress on outputs and outcomes. These indicators will help trace performance but refine programs, along with building evidence for replication. The framework will enlist all indicators that will be used to assess outputs, along with frequency of data collection and source of data collection. The steps to be followed include (a) developing the objectives of the program/innovation; (b) developing the logical framework; (c) outlining indicators for evaluating output and outcomes; (d) identifying methods and tools to get data on indicators; (e) developing tools for each indicator; (f) developing a Gantt chart for all implementation phases and project activities; (g) drafting an activity monitoring checklist and decide frequency for monitoring activities; (h) baseline data collection; (i) conducting and monitoring activities during the model implementation phase; (j) recurring assessments at different time intervals; (k) analysing data and disseminating project results.

### Quality control

The national coordinating unit at ICMR headquarters will conduct monthly online meetings with study site investigators to review overall progress and address any project administration issues. In addition, weekly meetings will also be held to assess data collection and evaluations, using REDCap data quality reports to ensure data integrity and consistency. To further strengthen quality assurance, the ICMR team will also undertake on-site monitoring visits ensuring training implementation and adherence to study protocols across all study sites.

## Statistical analysis

Quantitative analyses will be conducted using the IBM SPSS, while NVivo will be used for qualitative data analysis.

### Quantitative analysis

Data analysis would be done with IBM SPSS software (version 25.0) and R software (version 4.5.1). Nominal or categorical variables would be summarized as frequency and percentages. Continuous variables will be summarized as mean and standard deviation when normally distributed and as median and interquartile range (IQR) when non-normally distributed. Frequency and percentages will be used to describe categories of coverage (full/partial/not attempted), adoption, and reach of intervention within a cluster. The coverage will be compared across different categories (school types, study sites, urban/rural) using Chi-square test or fisher exact test.

Both clinical and implementation outcomes will be recorded as binary variables. Scores above or equal median will be considered as yes and below median as no for clinical outcomes while for implementation outcomes all the institutes will be evaluated as high performing (implemented 2 or more interventions) or low performing (implemented less than 2 interventions) based on the level of implementation. The study will employ the mixed effects logistic regression model within the generalized linear mixed models (GLMMs) framework to predict both types of binary outcomes, allowing for inclusion of both random and fixed effects. Covariates for assessing coverage of institutes will include type of institute; rural/urban location; gatekeeper to student ratio; youth champions to youth beneficiary ratio in modeling equation. For predicting help seeking behavior of students, covariates will include age and gender of student, education and occupation of parents, any known stressor in family such as recent death of close one; single parent; any past history of mental illness or suicide in family; etc.Time series analysis will be used for mathematical projection of the help seeking behavior of the youth beneficiaries in the study clusters. Forecasting model ARIMA (Autoregressive Integrated Moving Average) will be used to make projections till 12–18 months after the study period based on the data obtained at 3 time points (0, 6, 12 months).

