### Study setting

This study will be conducted in selected districts of eight states and union territories in India. The states and union territories are self-governing administrative divisions, and each of them has a state government. The administrative authority in these regions is shared among the state government and the central government. The study in each state and union territory shall be overseen by investigators belonging to a local institution. These states, union territories and institutions offering oversight include Andaman & Nicobar Islands (Andaman and Nicobar Islands Institute of Medical Sciences, Sri Vijaya Puram), Arunachal Pradesh (Rajiv Gandhi University, Papum Pare), Assam [All India Institute of Medical Sciences (AIIMS), Guwahati], Karnataka [National Institute of Mental Health and Neuro Sciences (NIMHANS), Bengaluru], Kerala (Government Medical College, Kollam), Maharashtra [Tata Institute of Social Sciences (TISS), Mumbai], New Delhi [Institute of Health Behaviour and Allied Sciences (IHBAS)], and Rajasthan [All India Institute of Medical Sciences (AIIMS), Jodhpur].

Within each state and union territory, one district has been selected for the study except for states of Arunachal Pradesh, Assam, Karnataka and Kerala. These include South Andaman (Andaman & Nicobar Islands); Dibang valley, Lower Dibang valley, Lohit, Papumpare, Itanagar capital complex, and Lower Subansiri (Arunachal Pradesh); Kamrup Urban/Rural (Assam); East Delhi (New Delhi); Bengaluru urban and rural (Karnataka); Thiruvananthapuram and Kollam (Kerala); Thane (Maharashtra) and Jodhpur (Rajasthan). These districts have been identified based on the reported suicide rate (3) and in consultation with respective state education and health departments. Intervention will be implemented at educational institutes in the selected districts. Educational institutes in all spheres including government aided, government-tribal aided and private funded shall be included in the study. The coordinating site would be the Indian Council for Medical Research (ICMR), Headquarters, New Delhi. The estimated time of completion of data collection will be December 2026, and the results are expected in March 2027.

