### Sample size for clusters

The unit of analysis in this multicentric study being cluster, the sample size for each site has been determined based on the presumption: anticipated intervention package adoption rate of 80%, a desired absolute precision of 10% and a 95% level of confidence. Based on these parameters each study site requires 64 (±5) institutes. Consequently, a total of 472–552 educational institutes will be included across the eight states and union territories.

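### Coverage is compared by urban/rural location and school type without stratifying by site, so differences between sites can appear as urban/rural differences

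*Protocol article*

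**What the plan says.** The Quantitative analysis section first treats coverage descriptively: "Frequency and percentages will be used to describe categories of coverage (full/partial/not attempted), adoption, and reach of intervention within a cluster". It then adds the tests: "The coverage will be compared across different categories (school types, study sites, urban/rural) using Chi-square test or fisher exact test". No stratification or adjustment is mentioned. The text does not say that sites are combined. That is the natural reading for school type and urban/rural, because study site is itself one of the compared categories.

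The next paragraph plans mixed effects logistic regression for binary outcomes, "allowing for inclusion of both random and fixed effects". For coverage: "Covariates for assessing coverage of institutes will include type of institute; rural/urban location", followed by the gatekeeper-to-student and champion-to-beneficiary ratios. Site is not in that list, and no grouping factor for the random effects is named. The binary implementation outcome in that paragraph is high versus low performing (two or more interventions implemented, or fewer), not the three-level coverage variable.

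On the design, Sample size for clusters states that "each study site requires 64 (±5) institutes" and that "a total of 472–552 educational institutes will be included across the eight states and union territories". Under Sampling method, each site lists its own institutes, stratifies them by type and samples in proportion to its own population. Study setting shows districts of different character: East Delhi alone for Delhi, both urban and rural Bengaluru for Karnataka, and six districts in Arunachal Pradesh. The limitations paragraph of the Discussion expects infrastructure, staff, practices and participant profiles to vary across sites.

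**The concern.** Site is a design stratum. A chi-square or Fisher test on a table that combines all sites treats institutes as exchangeable across them. That is harmless for the comparison between sites. For urban/rural, it confounds location with site whenever sites with more urban institutes also have systematically higher or lower coverage.

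A two-site example with assumed figures shows the mechanism. Site A is 90% urban with 87% coverage everywhere. Site B is 10% urban with 71% coverage everywhere. Neither site has any urban/rural difference. With equal numbers of institutes, combined urban coverage is 0.9 × 87 + 0.1 × 71 = 85.4% and combined rural coverage is 0.1 × 87 + 0.9 × 71 = 72.6%. The apparent gap of 12.8 points is entirely a site gap.

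At stake is the interpretation of an implementation result. A report that rural institutes achieved less coverage invites the reader to see rurality as the cause, when the cause may be one or two low-coverage sites. The crude test may also disagree with the mixed model on a closely related question.

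**Working it through.** **The plan's own figure.** Inputs, from Sample size for clusters: "anticipated intervention package adoption rate of 80%, a desired absolute precision of 10% and a 95% level of confidence".

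n = z² p(1 − p) / d² = 1.96² × 0.8 × 0.2 / 0.1² = 61.5, so 62 per site. The plan states 64, which is within 2. The totals match exactly: 8 × 59 = 472 and 8 × 69 = 552.

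**Simulation set-up**
- From the protocol: 8 sites, 64 institutes per site, and average coverage of about 80%. The last borrows the anticipated adoption rate, because no coverage rate is given.
- Assumed, because the protocol gives neither: the urban share in each site, and the SD of site coverage on the logit scale.
- Null: no urban/rural effect inside any site.
- Coverage is reduced to yes/no for simplicity.
- Tests: Pearson chi-square ignoring site, and Cochran-Mantel-Haenszel (CMH) stratified by site, both at two-sided 5%.
- 20,000 simulated studies per scenario. The Monte Carlo standard error near 5% is √(0.05 × 0.95 / 20,000) ≈ 0.15 percentage points.

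Scale of the SD: logit(0.80) = ln 4 = 1.386. An SD of 0.5 puts sites one SD either side of the centre at logits 0.886 and 1.886, that is 71% and 87%. An SD of 1.0 gives about 60% and 92%.

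**Rejection rate of the unstratified chi-square**

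| Urban share across sites | SD 0 | SD 0.25 | SD 0.5 | SD 1.0 |
|---|---|---|---|---|
| 50% in every site | 5.1% | 4.9% | 4.5% | 3.7% |
| 40–60% | 5.3% | 5.1% | 5.2% | 6.4% |
| 30–70% | 5.2% | 5.6% | 7.5% | 14.2% |
| 10–100% | 5.3% | 7.6% | 15.8% | 34.4% |

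The site-stratified CMH test stays between 4.7% and 5.5% in all 16 scenarios.

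Further runs at SDs of 0.3, 0.5 and 0.8 gave about 8–10%, 16% and 27–28% with shares over 10–100%, and about 5–9% with shares over 30–70%.

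**Reading the table.** The first column (no site difference in coverage) and the first row (same mix in every site) show no inflation. With the same mix everywhere, the test becomes slightly conservative as sites diverge. Inflation needs both differences and grows with each.

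**The case against.** **The crude test is followed by a model.** The next paragraph plans a mixed model for coverage with institute type and rural/urban location, so this can be read as a crude comparison followed by an adjusted one. The sequence is ordinary, but the model as written does not close the gap. Site is not among its covariates, no random-effect grouping is named, and its binary outcome is not three-level coverage. The chi-square is the only test stated for that variable.

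**A crude test answers a marginal question.** If rural institutes in the study have lower coverage overall, that difference is real even when site explains it. This stands. The term false positive applies only if the result is read as an urban/rural difference independent of site.

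**The tests carry little formal weight.** This also stands. No hypothesis, significance level or decision rule is attached to them, and coverage by location or type is neither a primary nor a secondary outcome. A reader might infer that they will decide where the model is scaled. The protocol does not say so.

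**The imbalance is assumed.** A reader might infer from the district list that urban/rural status is largely tied to site. No urban share is given for any site, and Bengaluru and Kamrup each name urban and rural areas within one site. Unequal mixes are plausible, but their extent is unknown.

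**School type is a weaker case.** Sampling is stratified by type within each site, which makes gross imbalance less evident. It does not make the mix equal, because allocation follows each site's own population. No school-type scenario was simulated separately.

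**Conclusion.** The concern holds conditionally. The protocol fixes tests of coverage by urban/rural and school type that ignore the site stratum, and the coverage model does not name site. If sites differ in both coverage and urban/rural mix, site differences can appear as urban/rural differences. The unstratified test then rejects in about 8–28% of studies for urban shares of 10–100% and site logit SDs of 0.3–0.8, and in about 5–9% for shares of 30–70%.

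It would be wrong to conclude that the error rate is above 5% in general. It is about 5% when site coverage is equal, and 3.7–5.1% when every site has the same mix. The figures rest on assumed shares and SDs, a dichotomised outcome and a null defined within site.

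The point affects the interpretation of an implementation measure and leaves the primary effectiveness analysis untouched. It is worth correcting because a better-matched method is available at almost no cost.

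**What to change.** Keep the chi-square or Fisher test for the comparison between study sites. For urban/rural and school type, choose one of two routes and state it:

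1. Test with a Cochran-Mantel-Haenszel test stratified by site. Coverage has three levels, so use the generalised form or specify a dichotomy in advance.
2. Label the crude comparisons descriptive and base inference on the planned coverage model, with site named as a fixed or random effect. State how that model's binary outcome relates to full, partial and not-attempted coverage. A fixed site effect is closest to the stratified test. A random site intercept still uses some between-site information on location.

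Neither route needs new data or a larger sample; the change is to the analysis wording and the choice of test form. The downside is that a site that is wholly urban or wholly rural contributes nothing to the stratified urban/rural comparison. That is appropriate, since such a site holds no within-site information on the question, but it may reduce precision. The report should therefore tabulate the number of urban and rural institutes by site.

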### Phases of study implementation

The study shall be carried out in three phases including Preparatory Phase, Phase I and Phase II as depicted in Table 2. The spirit figure of the phases is provided in Figure 2.

**Table 2 tab2:** Logic model for comprehensive mental well-being package scale up.

Phase	Preparatory phase	Phase 1	Phase 2
Duration (Months)	6	12 months	12–18 months
Key activities	Map and engage all leaders and policy makers (State and district education and health system) to gather support for adoption and implementation of intervention package in educational institutes Conduct workshops in sub sample of selected clusters (4–5 schools) to understand the barriers and enablers influencing adoption and adherence of intervention package	Minimum of 3 to 4 iterative cycles for model optimization with each cycle spanning for 2–3 months in 4–5 clusters of schools. Evaluation of implementation outcomes (Feasibility, utility, costing, sustainability and scalability) at baseline and at end of 2–3 months of implementation for each cluster Identification of barriers to service users -students and service providers-gatekeepers/DMHP	Implementation of Mref model Assessing risks of suicide behavior (perceived stress, depressive symptoms, low help-seeking) at baseline and at atleast at 6, 12 and 18 months Evaluation of implementation outcomes (Feasibility, utility, costing, sustainability and scalability) at baseline and at least at 6, 12 and 18 months
Key outcome	M0 + Model Mapping of stakeholders and resources Onboarding of Clusters Adaptation of measurement tools Developing SOPs for leaders/gatekeepers/youth champions/district mental health professionals	Mref Model Fine tuning of SOPs for leaders/gatekeepers/youth champions/district mental health professionals	Implementation of Mref. model in reducing suicide risk behavior in educational institutes

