#### Assessment time-points

The gatekeeper tools will be used at baseline (before gatekeeper training) and at 3 months intervals. In addition, all the tools except Gatekeeper help giving behaviors will also be used immediately after the training (post training assessment). Similarly, all the tools for youth champions and youth beneficiaries will be used at baseline (before the youth champion training) and subsequently at three-month intervals. In addition, these tools (except helping and help giving behaviors) will also be used immediately following the training for youth champions (post-training assessment). The general tools will be used at a three-month interval after the gatekeeper training and youth champion training are completed as described in Table 3.

**Table 3 tab3:** Description of study timelines for assessments.

Participant	Variables	T1 (Baseline)	T2 (4–6 months after T1)	T3 (12 months after T1)	T4 (18 months after T1)
Gatekeepers	Knowledge, Self-Efficacy, Intent to Ask	✓	✓	✓	✓
	Help-Giving Behaviors	✓	✓	✓	✓
Youth beneficiaries and youth champs	Depressive Symptoms (PHQ-9)	✓	✓	✓	✓
	Perceived Stress (PSS-10)	✓	✓	✓	✓
	Mental Health Awareness	✓	✓	✓	✓
	Help-Seeking Inclination (GHSQ)	✓	✓	✓	✓
	Help-Seeking Behavior	✓	✓	✓	✓
	Help Giving Behaviors	✓	✓	✓	✓
General	Acceptability, Appropriateness, Feasibility (AIM, IAM, FIM)	✗	✓	✗	✗
Exposure to program components and feedback	–	✗	✓	✓	✓
Semi-structured interviews (Barriers/Enablers)	IDIs/FGDs	✓	✓	✓	✓

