### Study outcomes

#### Primary outcomes

The present study focuses on the following primary outcomes:

Reduction in suicide risk factors: This is measured by a decrease in perceived stress levels and depressive symptoms among students in educational institutions using validated scales.Improvement in help-seeking behavior: This is measured by a rise in the proportion of individuals engaging with services/aid for mental health.

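### Three time points cannot support the planned ARIMA projection of help-seeking: the analyst's choice of differencing and drift would largely set the forecast

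*Protocol article*

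**What the plan says.** In the protocol article, Quantitative analysis sets out the projection in two sentences. The target is given as "Time series analysis will be used for mathematical projection of the help seeking behavior of the youth beneficiaries in the study clusters". The method named is ARIMA, and the horizon and input are stated as follows: "make projections till 12–18 months after the study period based on the data obtained at 3 time points (0, 6, 12 months". The section gives no model order, no longer or external series, and no model pooled across clusters.

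Help-seeking is one of the primary outcomes. Primary outcomes says of it: "This is measured by a rise in the proportion of individuals engaging with services/aid for mental health". The same Quantitative analysis section plans a separate mixed-effects logistic model for help-seeking.

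Other sections plan more assessments than the three used for the forecast:
- Table 2 (Phases of study implementation) lists "low help-seeking) at baseline and at atleast at 6, 12 and 18 months".
- Table 3 (Assessment time-points) has a fourth visit, "T4 (18 months after T1", and places the second visit 4–6 months after T1.
- The text above Table 3 says that the youth tools "will be used at baseline (before the youth champion training) and subsequently at three-month intervals".

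**The concern.** ARIMA learns its order, autocorrelation, drift and innovation variance from the history of one series. It therefore needs many regularly spaced points. Here the history is three points over 12 months, and the forecast must run at least another 12 months past the last of them. If the data cannot tell a series that reverts to its mean from one that stays level or keeps rising, whoever picks the order also picks the answer. Software will still print a forecast and an interval, and the interval can look precise. The Discussion says the study's results should inform policy, so a projection of this kind could mislead if it were used for that purpose.

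**Working it through.** The article gives no figure for this forecast, so there is none to reproduce. The check counts parameters, then compares forecasts on an assumed series.

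**Inputs from the article.** Observations at months 0, 6 and 12, so n = 3 and the step is 6 months. The horizon is 12–18 months after the study period. The order is not stated.

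**Step 1: parameter count.** Usable observations = 3 − d. Parameters k = p + q + (1 if there is a constant or drift) + 1 for the innovation variance. Residual df = (3 − d) − k. The small-sample information criterion AICc divides by (3 − d) − k − 1, so it needs that quantity to be positive.

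| Order | Usable obs. | k | Residual df | AICc denominator |
|---|---|---|---|---|
| (0,0,0) + constant | 3 | 2 | 1 | 0 |
| (1,0,0) + constant | 3 | 3 | 0 | −1 |
| (0,0,1) + constant | 3 | 3 | 0 | −1 |
| (0,1,0), random walk | 2 | 1 | 1 | 0 |
| (0,1,0) + drift | 2 | 2 | 0 | −1 |
| (1,1,0) | 2 | 2 | 0 | −1 |
| (0,1,1) | 2 | 2 | 0 | −1 |
| (1,1,0) + drift | 2 | 3 | −1 | −2 |
| (1,1,1) | 2 | 3 | −1 | −2 |
| (1,1,1) + drift | 2 | 4 | −2 | −3 |

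Every AR or MA order in the table is saturated or over-parameterised, and AICc is unusable throughout. The one exception by this count is an AR(1) or MA(1) with no constant and no differencing (3 − 2 = 1 df, AICc denominator 0). It forces the proportion back to zero, so it is not a serious candidate. None of these counts depends on the help-seeking rates.

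**Step 2: effect on the forecast.** The article gives no help-seeking rates, so 10%, 16% and 20% at months 0, 6 and 12 are assumed. Three steps (18 months) past month 12:
- ARIMA(1,0,0) with constant: about 15% (nominal 95% interval 7–23%). This is essentially the mean, (10 + 16 + 20)/3 = 15.3%.
- Random walk: 20%, the last value.
- Random walk with drift: the differences are 6 and 4 points, mean 5, so 20 + 3 × 5 = 35%.

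For the last of these, the SD of the two differences is √[(1² + 1²)/1] = 1.414 points. The standard error at h = 3 is 1.414 × √(h + h²/2) = 1.414 × √7.5 = 3.87 points. With t(0.975, 1 df) = 12.71, the half-width is 12.71 × 3.87 = 49 points.

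A second assumed series (20%, 26%, 29%) gives 25% with a constant mean, 29% with a random walk and 42.5% with drift. The drift interval there is ± 74 points.

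**Step 3: horizon.** If the study period ends at month 12, the projection runs to months 24–30, or (24 − 12)/6 = 2 to (30 − 12)/6 = 3 steps past the last input. If it ends at month 18, it runs to months 30–36, or 3 to 4 steps.

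**Step 4: would the fuller schedule help?** With month 18 added (4 points), AR(1) with constant has 4 − 3 = 1 df, a random walk with drift 3 − 2 = 1, and ARIMA(1,1,0) with drift 3 − 3 = 0. Three-monthly data to month 18 would give 7 points and 4, 4 and 3 df. That is still too short a series to identify an order or to forecast several steps ahead.

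**The case against.** The projection is supplementary. The primary outcome is the observed rise in help-seeking, which has its own mixed-effects logistic model. No sample size, listed outcome or stated success criterion uses the forecast. This stands, and it limits the severity.

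It is tempting to say that the model cannot be estimated at all, or that the forecast carries no information from the data. Neither holds in full. The constant mean, random walk and random walk with drift all return output that uses the observations. On the assumed series, the differenced orders with drift agree closely at three steps (35.0% to 35.8%). The disagreement comes from whether to difference and whether to include drift: ARIMA(1,1,0) without drift gives about 30%. Three points cannot justify that choice.

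A reader might also cite the very narrow interval that software prints for ARIMA(1,1,0) with drift as proof that the models contradict each other. That fit does not converge, and its interval changes with the units: about 34.8–36.7% with proportions entered, 35.95–36.05% with percentages. It should not be used as evidence.

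A reader might infer that the forecast is going to be put before policy makers as the expected course of a primary outcome. The Discussion speaks only of the study's results in general, so the most one can say is that it could mislead if used that way.

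The visits cannot simply be called irregular either. Table 3 allows 4–6 months for the second visit, but Table 2 has regular six-monthly visits and the text has three-monthly ones.

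Finally, many students and about 64 institutes per site make each proportion more precise, but they add no time points. A model pooled across clusters could borrow strength, but none is described, and time would still be seen on only three occasions.

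**Conclusion.** The projection is wrong as written and should be fixed. The article itself fixes both the method and the three-point input, so no order chosen later in an analysis plan would repair it. The data cannot select an order, and the choice of differencing and drift largely sets the result. On the assumed series of 10%, 16% and 20%, the projection moves from about 15% to 35% at three steps, and the 1-df interval for the drift model is too wide to use. The percentages rest on assumed rates; the degrees-of-freedom counts do not. The forecast also leaves out planned data (month 18, and the three-monthly assessments if those are carried out), although using them would not rescue it. The fault is confined to the projection.

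**What to change.** Delete the ARIMA sentence and the time-series sentence that introduces it. In their place, state that help-seeking at each planned visit, and its change from baseline, will be reported with 95% confidence intervals from the mixed-effects logistic model already planned, with visit entered as a factor. Use all planned visits, including month 18, and reconcile the three descriptions of the visit schedule so that the model's visits are defined.

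If a projection is still wanted, present it only as labelled exploratory scenarios, for example that the change persists, wanes, or returns to baseline. It should not appear as a fitted time-series forecast with an interval.

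The cost is a change of wording in the analysis section and the loss of one unsupported forecast. Data collection and sample size do not change.
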